##### Treatment and evaluation phase

Both the treatment and placebo-control groups will be hospitalised for 4 days, and after a washout period of over 4 weeks the participants will be hospitalised again for 4 days. During hospitalisation, subjects will be administered GJD or placebo (one pill twice a day 30 min before breakfast and dinner) for 3 days. Group A participants will be administered GJD in phase I, followed by placebo treatment in phase II (both treatments will be administered twice daily for 3 days each). Group B participants will be administered placebo in phase I, followed by GJD treatment in phase II (same regimen as in group A; Fig. 1). To assess the effects of GJD treatment, participants will be allowed to sleep for only 4 h (02:00 to 06:00) on days 2 and 3 to artificially induce fatigue, and will carry out various activities such as walking, taking lectures, and watching movies to limit daytime sleep. To control possible bias, all subjects will be limited to intensive exercise and will consume the same foods during the study periods.

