### Randomisation and allocation concealment

Randomisation codes will be generated through block randomisation in a 1:1 code for groups A (phase I: GJD, phase II: placebo) and B (phase I: placebo, phase II: GJD). For the generation of a randomisation code, Random Allocation Software program v2.0.0 (M. Saghaei, MD, Department of Anaesthesia, Isfahan University of Medical Sciences, Isfahan, Iran) will be used.

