### Sample size

No previous clinical trials for serum cortisol levels from which sample size could be calculated have been reported; however, we consider a sample size of 24 to be a practical number for detection of clinically important differences between treatment and control groups. This number of subjects (12 per group) is the recommended minimum number per group for pilot studies [23]. We judged that this pilot study recommendation is applicable to feasibility study described here. Based on the results of this study, pilot trials will be needed in order to calculate appropriate sample size.

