The primary outcome analysis (*Δ = D*_*GJD*_*– D*_*PL*_) will be performed in two stages. First, a linear mixed effect model will be applied to assess the effect of treatment, sequence, and period with the random effect for subjects. The carryover effect due to preceding the treatment stage will then be estimated by testing the effect of sequence in the model. The linear mixed model will be modified by confounding the sequence effect to the error term if the carryover effect is not significant. Otherwise, the model will be rebuilt based on data collected in the first phase of the study. An analysis of variance (ANOVA) table for the model will be provided and least square means and their standard errors (95 % confidence intervals) will be reported for each treatment. Second, if the structure of data is balanced and the carryover effect is invalid, simple paired two-sample *t* tests or Mann Whitney *U* tests will be performed to evaluate the effect of GJD. The results will be shown as means and standard deviations for each treatment group and mean differences between the two treatments (95 % confidence interval) will be reported.

The analysis of secondary outcomes will be focussed on changes of measures within each treatment group from the baseline to the end of study. Again, the linear mixed effect model will be applied. The level of significance will be set to 0.05 (two-tailed) and all analyses will be performed with PROC MIXED and PROC GLM in SAS software, version 9.4 (SAS Institute Inc., Cary, NC, USA).

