This is a feasibility study and is, thus, not powered to determine treatment effectiveness. As appropriate sample size could not be determined due to a lack of similar previous studies, the minimal sample size considered clinically significant was defined. The results of this study may, therefore, affect generalisability in other environments. Moreover, because fatigue will be artificially induced in healthy people in this study, the findings would not represent chronic fatigue, which is more clinically relevant. Further study with exact sample sizes in patients complaining of chronic fatigue would be necessary and could be designed based on the results from this study. This study protocol represents a unique opportunity to enhance our understanding of fatigue and the effects GJD on fatigue in terms of endocrine and immunological mechanisms and may, therefore, serve to improve future treatment strategies for chronic fatigue.

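### The carryover pre-test with a phase I fallback raises the primary analysis's type I error to about 6 to 8% instead of the stated 5%

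*Protocol article*

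**What the plan says.** The primary outcome is the change in serum cortisol from day 2 to day 4 within each phase. The Statistical analysis section fits a linear mixed model with treatment, sequence, period and a random subject effect, and then applies a two-way rule:

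- The test: "The carryover effect due to preceding the treatment stage will then be estimated by testing the effect of sequence in the model".
- If it is not significant: "The linear mixed model will be modified by confounding the sequence effect to the error term if the carryover effect is not significant". Both phases are used.
- If it is significant: "Otherwise, the model will be rebuilt based on data collected in the first phase of the study".

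The only significance level given is 0.05, two-tailed. No separate level is set for the carryover test, and nothing is adjusted for the choice it drives.

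On design, the Sample size section gives 24 participants, 12 per sequence group, and allocation is 1:1. Dosing lasts 3 days per phase, and "after a washout period of over 4 weeks the participants will be hospitalised again for 4 days". The Discussion adds: "This is a feasibility study and is, thus, not powered to determine treatment effectiveness".

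**The concern.** The sequence test compares each participant's total over the two phases between groups. The fallback compares the phase I values between the same groups. Phase I is half of that total, so a chance imbalance in phase I makes the pre-test more likely to be significant and then becomes the result that is reported. The phase I test is judged against 0.05 as if it had not been selected in this way.

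The pre-test also does not isolate what it is meant to detect. The design yields four sequence-by-phase means. Once the overall mean, period and treatment are fitted, one contrast remains, and it carries carryover, chance differences between the groups and treatment-by-period interaction together.

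At stake are the stated 0.05 for the primary outcome and, when the fallback fires, the precision of the estimate that later trials would be planned from.

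**Working it through.** **Inputs from the protocol article.** 12 per sequence; two-sided 0.05 for every test, including the pre-test; the rule above.

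**Assumptions.** Change scores are normal with SD 1 in each phase, so effects are in SD units. The between-phase correlation rho is not given and is taken as 0 to 0.75.

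**1. The plan's own figure.** If the crossover model is always used, simulated type I error is 4.9 to 5.1% at every correlation tried. The stated 0.05 is delivered when there is no pre-test.

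**2. Overlap of the two tests.** Let D be the phase I difference between groups and S the difference in subject totals.
- Var(D) = 2/12 = 0.167, so SD(D) = 0.41.
- Var(S) = 2(1+rho) × 2/12 = (1+rho)/3.
- Corr(D, S) = (1+rho)/sqrt(2(1+rho)) = sqrt((1+rho)/2), which is 0.71 at rho 0 and 0.94 at rho 0.75.

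**3. Overall type I error with no effect and no carryover.** Totals and within-subject differences are independent here, so the crossover branch contributes 0.95 × 0.05 = 0.0475. The fallback branch contributes 0.05 times the false rejection rate of phase I given a significant pre-test, which was simulated.

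| rho | Phase I rejection given fallback | Overall error |
|---|---|---|
| 0 | 32% | 0.0475 + 0.05 × 0.32 = 6.4% |
| 0.25 | 41% | 0.0475 + 0.05 × 0.41 = 6.8% |
| 0.5 | 51% | 0.0475 + 0.05 × 0.51 = 7.3% |
| 0.75 | 66% | 0.0475 + 0.05 × 0.66 = 8.1% |

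Direct simulation of the whole rule agrees: 6.3 to 6.5% at rho 0, rising to 8.1% at rho 0.75. The ceiling, if the phase I test always rejected in the fallback, is 0.0475 + 0.05 = 9.75%.

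**4. The fallback estimate.** The regression slope of D on S is [(1+rho)/6] / [(1+rho)/3] = 1/2. So the mean of D in the fallback, minus the true effect, is half of (mean of S in the fallback minus the true carryover).
- Without carryover, S is symmetric about 0 and the two-sided selection keeps it so. The estimate is centred on the truth: simulated means were 0.78 to 0.81 for a true 0.8. Its SD is 0.72 to 0.88, against 0.41 without selection.
- With real carryover, selection on significance pushes S beyond its true value, and half of that excess passes into D as bias.

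**5. Power of the pre-test.** The noncentrality is carryover / sqrt((1+rho)/3), on 22 degrees of freedom.
- Carryover 0.5 SD: 0.5/0.577 = 0.87 at rho 0, power 13%; 0.5/0.764 = 0.65 at rho 0.75, power 10%.
- Carryover 1 SD: 1.73 at rho 0, power 38%; 1.31 at rho 0.75, power 24%.

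**6. Phase I alone, unconditionally.** A crossover with 80% power has noncentrality 2.93 on 22 degrees of freedom. Phase I alone has 2.93 × sqrt((1-rho)/2): 2.07 at rho 0, 1.47 at 0.5 and 1.04 at 0.75. The powers are 51%, 29% and 17%. These describe phase I data as such, not phase I after a significant pre-test.

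**The case against.** The strongest reply is that little rests on this. The study calls itself a feasibility trial not powered for effectiveness, and further pilots are planned before a sample size is set. After 3 days of dosing and a washout of over 4 weeks, carryover is unlikely, so the fallback would fire in about 5% of trials and the crossover would survive in the other 95%. The excess error is about 1.3 to 3.1 percentage points, and the overall loss of power at a true 0.8 SD is only about 1 to 2.5 points. All of this stands and lowers the severity. It does not remove the point, because the article still makes a 0.05 test of cortisol its primary analysis and prescribes a rule that misses that level.

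A second reply is that carryover must be guarded against. The guard is weak. With no treatment effect and a carryover of 0.5 SD, the rule rejects in 14 to 32% of trials (rho 0 to 0.7) and the unguarded crossover in 13 to 32%, so there is no gain. At 1 SD the rule does help, with 27 to 67% against 38 to 85%, but it is still far from 5%. Protection has to come from the washout.

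Two stronger readings are tempting. A reader might infer that the fallback estimate is always biased. Step 4 shows that without carryover it is over-dispersed but centred on the truth. A reader might also take 32 to 66% as the trial's false positive rate. That figure applies only inside the fallback, and between a third and two thirds of chance-triggered fallbacks show no significant phase I difference.

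**Conclusion.** The point holds and should be fixed. As written, the primary analysis has an overall two-sided type I error of about 6.3 to 8.1% rather than 5%, under normal change scores with equal variances, 12 per sequence, a 0.05 pre-test and a between-phase correlation assumed between 0 and 0.75. The inflation is moderate overall and severe within the fallback, where large chance differences are over-represented. The pre-test that triggers it has little power for carryover and cannot identify it. The article gives no SD, effect size or correlation for cortisol change, so the power figures are illustrative, in SD units. The documents do not support saying that the crossover is generally discarded or that the trial's conclusions are invalid: the phase I analysis replaces it only after a significant sequence test, and the study makes no claim to be powered for effectiveness.

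**What to change.** - Delete the sequence pre-test and the phase I fallback.
- Name one primary analysis: the mixed model with fixed treatment, period and sequence and random subject, on all data from both phases. With balanced, complete data, keeping the sequence term does not change the treatment comparison.
- Remove the dependence on the carryover result from the second-stage paired comparison as well.
- State that absence of carryover is assumed on the strength of the washout of over 4 weeks after 3 days of dosing, and describe the day 2 baselines by phase and sequence so that readers can judge it.
- Report any phase I-only estimate as descriptive, with its confidence interval and no role in the primary conclusion.

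The cost is a change of statistical wording, with no extra data or participants. In simulation without carryover it restores the error rate to 4.9 to 5.1%. In exchange, the crossover estimate is openly conditional on the washout having worked.

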### Design and setting

This randomised, double-blind (both patient and practitioner or assessor), placebo-controlled crossover clinical trial will be conducted in Republic of Korea.

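### Stage 2 of the primary analysis names the Mann-Whitney U test, an independent-samples test, for paired crossover data; its size and power are off to the extent that the two change scores correlate within a man

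*Protocol article*

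**What the plan says.** The trial is a two-phase crossover in 24 men. The article's Treatment and evaluation phase section has group A take GJD then placebo and group B placebo then GJD, so each man yields one change score under each treatment.

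Under Statistical analysis, the primary variable is the end-point serum cortisol minus the day 2 baseline of the same phase, formed separately for GJD and placebo. The analysis then has two stages.

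- Stage 1: "a linear mixed effect model will be applied to assess the effect of treatment, sequence, and period with the random effect for subjects".
- Stage 2 applies "if the structure of data is balanced and the carryover effect is invalid". Then "simple paired two-sample *t* tests or Mann Whitney *U* tests will be performed to evaluate the effect of GJD".

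Stage 2 results are to be reported by treatment group and as a mean difference between treatments with a 95% confidence interval. Both stages are described as parts of the primary outcome analysis, at a two-sided level of 0.05.

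**The concern.** The Mann-Whitney U test compares two independent samples. Offered as the alternative to a paired t test, with results shown by treatment, it reads as a comparison of 24 GJD values with 24 placebo values from the same 24 men. That ignores the pairing which is the reason for a crossover. The same section uses the rank-sum test correctly for the baseline comparison, where the two sequence groups really are independent.

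At stake is a stage 2 p-value that may be too large for the evidence and may disagree with the stage 1 model. A smaller point is that stage 2 has no period term, although stage 1 has one.

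**Working it through.** **Inputs from the article.** Sample size: "we consider a sample size of 24 to be a practical number", that is 12 per sequence. Allocation: "Randomisation codes will be generated through block randomisation in a 1:1 code". Two-sided alpha 0.05. The article gives no effect size, standard deviation, correlation or power, so there is no figure of its own to reproduce.

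**Assumptions.** Normal change scores with common SD σ; within-man correlation ρ between the GJD and placebo change scores; any period effect on the change score. None of these is in the article.

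**Step 1: why the size moves.** With n = 24 pairs, the variance of the difference in means is 2σ²(1−ρ)/n. An unpaired test takes it to be 2σ²/n. Under the null its standardised statistic therefore has SD √(1−ρ), and approximately

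size = P(|Z| > 1.96/√(1−ρ)).

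- ρ = 0: 1.96/1 = 1.96, size 5.0%
- ρ = 0.25: 1.96/0.866 = 2.26, size 2.4%
- ρ = 0.5: 1.96/0.707 = 2.77, size 0.6%
- ρ = −0.3: 1.96/1.140 = 1.72, size 8.6%

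This is a large-sample guide based on means. The rank test itself was simulated.

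**Step 2: simulated Mann-Whitney on 24 GJD versus 24 placebo values, no period effect.** Power is taken at the effect for which the paired t test has 80%.

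| ρ | True size (nominal 5%) | Power (paired t 80%) |
|---|---|---|
| 0 | about 5% | 79% |
| 0.1 | 3.6% | 75% |
| 0.25 | 2.5% | 70% |
| 0.5 | 0.9% | 50% |
| 0.75 | 0.05% | 17% |

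Repeat simulations agree to about half a percentage point on size and one point on power. At ρ = −0.3 the simulated size is 8.0%, so inflation needs a negative correlation.

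**Step 3: which ρ is relevant.** It is the correlation between change scores, not between raw cortisol values. Write each value as a stable man-specific level s plus independent error. Then C(GJD) = (s + e₁) − (s + e₂) and C(PL) = (s + e₃) − (s + e₄). The level s cancels from both, so their covariance is 0. Simulating raw cortisol with correlation 0.75 under this model gives a change-score correlation of about 0.00 and a Mann-Whitney size of about 4.5%. A positive ρ needs a response to sleep loss that repeats within a man from one phase to the next.

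**Step 4: leaving out period.** With 12 men per sequence, a period effect of π (in units of σ) enters the within-man treatment difference with opposite sign in the two groups. It cancels from the mean but inflates the variance by the factor 1 + π²(24/23)/[2(1−ρ)]. At ρ = 0.5:

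- π = 0.5: 1 + 0.25 × 1.0435/1 = 1.26
- π = 1: 1 + 1 × 1.0435/1 = 2.04

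In simulation the paired t size falls from 5.1% to 2.8% and 0.6%, and power from 77% to 69% and 45%. The period-adjusted t test keeps about 76%.

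**Step 5: the replacements.** With no period effect and at every ρ tried, the rank-sum test on phase differences between sequences has size 4.4% to 4.7%, and the Wilcoxon signed-rank test 4.7% to 5.1%. At an effect where the paired t test has about 76% power, they have 72% to 73% and 74% to 75%. With a period effect of 0.5 to 1 SD, the rank-sum version keeps size 4.2% to 4.7%, while signed-rank becomes conservative as the paired t does.

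**The case against.** **Stage 1 is sound.** The mixed model carries treatment, sequence, period and a random subject effect, and reports least-squares means with intervals. Stage 2 is a conditional second step whose reported estimate is a mean difference. This stands and limits the point to stage 2.

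**The correlation may be near zero.** Step 3 supports this. A reader might infer that a non-parametric primary result must have wrong error rates, and quote the 17% power. The documents do not support that: they give no correlation, and 0.75 for change scores is the far end of an assumed range.

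**The error is conservative for positive correlation, and the article says the trial is not powered for effectiveness.** Both are true. A reader might take a wrong test to mean more false positives; that would need a negative correlation.

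**Mann-Whitney can be valid in a crossover,** when applied to phase differences between sequence groups, and a condensed article may have shortened that. But the text pairs the test with a paired t test, reports by treatment and mentions no phase differences. The literal reading remains the natural one.

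**No trigger for U is stated.** It is tempting to say that non-normal cortisol leads to the U test. The Shapiro-Wilk test appears with the baseline summaries and is not tied to this choice, so that link is an inference.

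**Omitting period is harmless under balance.** Largely so: stage 2 requires balanced data, the estimate is then unbiased, and power suffers only if a period effect on the change score exists. A constant shift across a whole phase would cancel from the change.

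**Conclusion.** The point holds in a limited form: as written, stage 2 names an independent-samples test for paired data. How much this matters depends on an unknown correlation between change scores. At 0 there is almost no loss (79% against 80% power), at 0.25 about 10 points, at 0.5 about 30, and at 0.75 about 63 (80 − 17). These figures assume normal change scores, 24 complete pairs and no period effect.

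For positive correlation the consequence is a missed effect in stage 2 and possible disagreement with stage 1, not a raised false-positive rate. The stage 1 result does not depend on it. The missing period term is a lesser matter of efficiency. This is a wording error worth correcting before the data are analysed; it does not undermine the design or the main model.

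**What to change.** Amend the stage 2 wording as follows.

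1. State that the stage 1 mixed model with period decides the primary outcome and that stage 2 is supportive.
2. Replace the Mann-Whitney wording by a rank-sum test comparing sequence groups A and B on each man's phase I minus phase II difference in change score, with a Hodges-Lehmann interval. With treatment effect τ and phase effect p, the expected difference is p + τ in group A and p − τ in group B. The phase effect cancels between groups and the shift is 2τ, so the estimate and interval are halved to give τ.
3. If something simpler is preferred, the Wilcoxon signed-rank test on the within-man GJD minus placebo differences is acceptable. It respects the pairing but, like the paired t test, does not adjust for period, and the text should say so.

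The cost is a sentence or two of analysis wording. No additional data, men or assessments are needed.

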## Methods

### Objective

The aim of this study was to develop a protocol to (1) evaluate the anti-fatigue effects of GJD in acute fatigue; (2) verify the mechanisms underlying the observed effects by assessing changes in stress hormones, oxidative stress-related biomarkers, homocysteine, and immunological factors; and (3) clinically assess the effectiveness and safety of GJD in treating acute fatigue using the Korean version of the Fatigue Severity Scale (FSS-K), Brief Fatigue Inventory (BFI-K), and Leeds Sleep Evaluation Questionnaire (KMLSEQ) scores as well as carrying out daily fatigue and sleep evaluations and assessments of heart rate variability (HRV) and adverse events.

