**Fig. 1 Fig1:**
[figure not shown]
Flowchart describing the study plan

Blood samples will be collected at 06:30 for analysis of serum cortisol, stress hormones, oxidative stress-related biomarkers, homocysteine, and immunological factors. Saliva samples will be collected at 06:30, 12:00, and 21:00 for analysis of salivary cortisol, while HRV will be assessed at 15:00–17:00. Self-reporting of FSS-K, BFI-K, KMLSEQ, and daily fatigue and sleep status will be carried out via questionnaires after dinner on days 1, 2, 3, and 4.

After a 4-week washout period, participants will be admitted to phase II for 4 days, during which they will undergo the same schedule.

The schedule of events for the trial is outlined in Table 1 and the study participants’ timeline of activities, treatments, and assessments during hospitalisation is shown in Fig. 2.

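### The secondary analysis states within-treatment change as its focus and names no GJD minus placebo contrast, so it cannot separate GJD from the sleep restriction imposed under both treatments

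*Protocol article*

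**What the plan says.** All of the analysis text is in the Statistical analysis section of the protocol article.

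- **Primary outcome (serum cortisol).** Change is computed under each treatment, and the target is the GJD value minus the placebo value. The model is set out: "a linear mixed effect model will be applied to assess the effect of treatment, sequence, and period with the random effect for subjects". For the second-stage analysis, "mean differences between the two treatments (95 % confidence interval) will be reported".
- **Secondary outcomes.** "The analysis of secondary outcomes will be focussed on changes of measures within each treatment group from the baseline to the end of study". Then: "Again, the linear mixed effect model will be applied". No difference between treatments is named as the quantity to be estimated or tested.

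Two other places bear on this. Under Treatment and evaluation phase, "participants will be allowed to sleep for only 4 h (02:00 to 06:00) on days 2 and 3 to artificially induce fatigue". The text after Fig. 1 says of the second admission that "participants will be admitted to phase II for 4 days, during which they will undergo the same schedule". Each man therefore has the same sleep restriction once under GJD and once under placebo.

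The Objective section gives the secondary outcomes their purpose. Objective 2 is to "verify the mechanisms underlying the observed effects by assessing changes in stress hormones, oxidative stress-related biomarkers, homocysteine, and immunological factors". Objective 3 covers the fatigue and sleep questionnaires, heart rate variability (HRV) and adverse events.

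**The concern.** The trial provokes the response that it measures. The article's Discussion itself cites reports that oxidative markers, antioxidant levels and autonomic measures differ or shift with fatigue. These measures can therefore be expected to move between baseline and the end of a phase even if GJD does nothing. A change within the GJD condition is the sum of three things: any drug effect, the effect of sleep restriction, and any other time effect of a four-day admission. Only the comparison with placebo removes the last two, and the randomised, blinded crossover exists to supply that comparison.

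If the analysis follows the stated focus, a significant change under GJD could be presented as an anti-fatigue effect or a verified mechanism when it is only the time course of short sleep. Low power in a feasibility trial is a different problem. It limits precision, whereas a within-treatment change fails to isolate GJD at any sample size.

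**Working it through.** **1. The two paragraphs side by side.** For the primary outcome the section gives the response (change under each treatment), the target (their difference), the model, and a mean difference with confidence interval. For the secondary outcomes it gives the response (change within each treatment group) and a model, but no target difference. A model with a treatment term can produce each treatment's least-squares mean change or the difference between the two. The only sentence that says which is of interest points to the former.

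**2. Inputs.**

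- From the article: 24 participants, 12 per sequence, each receiving both treatments; two-sided level 0.05; the same sleep restriction in both phases.
- Not in the article: any SD, effect size or power. The sample size is a pilot-study minimum (2 × 12 = 24), so there is no power figure to reproduce.
- Assumed: GJD effect zero; complete data; normal change scores; a common shift *s* from sleep restriction, in SDs of the change score, from 0 to 1.0; correlation between a man's two changes of 0, 0.3 or 0.5.

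**3. Test of change within GJD.** The simplest form is a one-sample *t* test with n = 24 and 23 df. With *c* the 97.5% point of *t* on 23 df, the chance of significance is

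P = 1 − F(c; 23, s√24) + F(−c; 23, s√24),

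where F is the noncentral *t* distribution function. For example, at s = 0.5 the noncentrality is 0.5 × √24 = 2.45 and P = 0.650.

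**4. Between-treatment contrast.** Let *d* be the GJD change minus the placebo change for each man. The period-adjusted estimate is (mean *d* in group A + mean *d* in group B)/2, with standard error (pooled SD of *d*) × √(1/24) and 22 df. With no drug effect the expected value of *d* is s − s = 0 apart from a period effect. A period effect enters the two groups with opposite signs and cancels. The rejection rate was simulated, 50,000 runs per setting.

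| Shift *s* (SD) | s√24 | Within-GJD change significant | GJD minus placebo significant (range over the three correlations) |
|---|---|---|---|
| 0 | 0 | 0.050 | 0.051 |
| 0.2 | 0.98 | 0.156 | 0.048–0.050 |
| 0.3 | 1.47 | 0.291 | 0.048–0.052 |
| 0.5 | 2.45 | 0.650 | 0.048–0.051 |
| 0.8 | 3.92 | 0.963 | 0.050–0.051 |
| 1.0 | 4.90 | 0.997 | 0.048–0.049 |

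The within-GJD test responds to the shift that both treatments share. The contrast stays at its nominal level whatever that shift is.

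**The case against.** The strongest reply is that "Again, the linear mixed effect model will be applied" points back to the only mixed model described, which has a treatment term. On this reading, the preceding sentence merely names the response variable, much as change is first computed within each treatment for cortisol and then compared. A model with treatment, sequence and period terms would also be an odd tool for separate tests within each arm.

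This reading is plausible, and part of it stands: the intended analysis may well contain the right comparison. It does not settle the matter, because the text never says that the treatment difference is what will be estimated or reported for these outcomes. If the contrast was meant, the sentence misdescribes it and still needs correcting.

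A reader might also infer more than the article supports:

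- *That the placebo comparison is used for cortisol only.* The article does not say so. It leaves the reported contrast for secondary outcomes unnamed.
- *That GJD will be declared effective when its change is significant and the placebo change is not.* No such rule appears. If someone applied it with no drug effect, the pattern would arise in about 16% to 23% of cases at a shift of 0.5 SD, for correlations of 0.5 down to 0. The top figure treats the two conditions as independent, although the same men supply both.
- *That objectives 2 and 3 would go wholly unanswered.* Serum cortisol is listed among the stress hormones in the footnote to Table 1 and has an explicit contrast. Objective 3 also includes safety. Neither depends on this sentence.
- *That the number of secondary variables is part of the fault.* Multiplicity is a separate question, commonly left to the analysis plan, which is not shown.

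**Conclusion.** The point holds as a defect in the stated analysis of the secondary outcomes. The declared focus cannot isolate a GJD effect, and no between-treatment comparison is named to do so. This affects the secondary-outcome parts of objectives 2 and 3: catecholamines, oxidative and immune markers, questionnaires and HRV.

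For a shift of 0.3 to 0.8 SD with no drug effect, a within-GJD test would be significant about 29% to 96% of the time, where the contrast gives about 5%. These figures rest on an assumed shift and on reading the focus as a test of change within GJD. With no shift the within-GJD rate is also 5%, so the size of the problem depends on how strongly sleep restriction moves each measure. That the two effects are mixed does not depend on those assumptions.

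**What to change.** Replace the sentence on secondary outcomes with one to this effect: each secondary outcome will be analysed as the GJD minus placebo difference in change from that phase's own baseline, reported with a 95% confidence interval, from the planned linear mixed model with treatment, period and random subject effects; changes within each treatment will be shown descriptively only.

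Defining baseline and end point within each phase also removes a looseness in the present text: in a two-phase crossover, a span from baseline to the end of the study could be read as covering both treatments.

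The cost is a change of wording. The model is already planned and the data are already to be collected. No procedure, assessment or participant is added.
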